## Abstract

**Background:**

Universal coverage of long-lasting insecticidal nets (LNs) made from polyester or polyethylene fibres has been adopted as the standard of care to control malaria among at-risk populations. To obtain a WHO recommendation, LNs must undergo prospective monitoring of insecticidal efficacy against mosquito vectors over 3 years of household use. The retention of bioefficacy and physical durability of a LN is influenced by net usage practices, textile polymer material and insecticide treatment technology. Fabric durability is the critical factor which determines the interval required between LN replacement campaigns. To investigate factors known to affect LN durability and bioefficacy, we describe a three-arm WHO Pesticide Evaluation Scheme (WHOPES) Phase III evaluation of a LN made uniquely from polypropylene (LifeNet®, Bayer CropScience) compared to standard LNs made from polyester and polyethylene, all treated with deltamethrin, over 3 years of use.

**Methods:**

This is a prospective three-arm household randomized, equivalence trial of LNs in Tanzania, with nets as the unit of observation. Equal numbers of houses will be randomized to receive deltamethrin-treated polypropylene, polyester or polyethylene LNs; all sleeping spaces in a given household will be provided with one type of net. Bioefficacy (insecticidal activity against mosquitoes), insecticide content of net fibres, and fabric integrity (number, location and size of holes) will be measured every 6 months, using WHO cone or tunnel bioassays, chemical analysis and calculation of hole index, respectively. A cohort of LNs will be surveyed annually to assess survivorship (median LN survival time) and cumulative loss of fabric integrity. Field durability outcomes will be compared with laboratory strength tests.

**Discussion:**

This is the first trial to compare the relative durability of three LNs each made from a different textile polymer, treated with the same insecticide, in the same community side-by-side over 3 years of use. Trial findings will 1) guide global health organizations on procurement policy and the type of textile polymer which maximizes the interval between LN replacement campaigns, and 2) stimulate manufacturers to improve product performance and development of longer lasting polymers. A full WHO recommendation may be granted to LifeNet® upon successful Phase III completion.

## Background

Long-lasting insecticidal nets (LNs) are one of the key measures recommended by the World Health Organization (WHO) for prevention and control of malaria [1]. While considerable progress has been made by many National Malaria Control Programs (NMCPs) and international donor agencies to facilitate free or subsidized universal coverage campaigns (UCCs) for at-risk populations [2], of increasing concern is how to prolong effective life and field durability of LNs in order to extend the interval between UCCs and improve cost-effectiveness [3].

In recent years, the WHO has developed guidelines to assess the insecticidal efficacy of LNs, net durability and survivorship under operational conditions [4–6]. New LNs are granted a WHO Pesticide Evaluation Scheme (WHOPES) time-limited interim recommendation for use following successful evaluations in laboratory conditions (Phase I) and in small-scale field trials in experimental huts (Phase II), during which a product must retain insecticidal activity for at least 20 standardized washes with respect to vector knock-down, mortality and blood-feeding inhibition [7, 8]. To receive a full WHO recommendation, LNs are required to undergo prospective insecticidal efficacy and net durability monitoring over 3 years of household use (Phase III) [7, 8]. LN durability is measured as a function of net survivorship, fabric integrity and insecticidal activity [4], which are all influenced by frequency of use, net care and repair, washing and maintenance practices, duration of transmission season [9–11], as well as the textile’s physical features, such as fibre material, knitting or weaving pattern, insecticide type and concentration, and fibre impregnation technology [12]. Average effective net life is often assumed to be 3 years [4] but can vary substantially between products [13, 14], endemic regions [15–19], and conditions of use [20].

The potential market for LNs in Tanzania, as in all African malaria endemic countries, is large and significant [1, 21]. Since 2004, the NMCP in Tanzania, supported by the Global Fund to Fight AIDS, Tuberculosis and Malaria (GFATM), has scaled up the distribution of LNs through a range of public and private sector mechanisms [22], most notably the Under Five Coverage Campaign launched in 2008 [23] and the UCCs of 2010-11 and 2015-16 to provide full coverage in all households at risk of malaria [24].

While a WHOPES Phase III recommendation is based primarily on insecticidal efficacy over time, the physical durability of the fabric is the main factor determining the lifespan of a typical LN. Durability is influenced by fibre denier, the bursting strength of the net, the knitting pattern and the polymer material [12]. All brands of LN in regular use are made from either polyester (43%) or polyethylene (57%) [25]. LifeNet® (Bayer CropScience, Germany) is a new deltamethrin-impregnated long-lasting net (LN), uniquely made from polypropylene knitted fibres, which received interim WHOPES recommendation in 2011 following successful Phase I and Phase II trials [26, 27]. According to the manufacturer the main advantage over standard polyester and polyethylene LNs is its improved durability for household use [26]. To investigate factors known to affect LN durability, here we describe the study design and methodology of a large scale community-based Phase III evaluation of LifeNet® LN compared to two WHOPES recommended LNs made from polyester and polyethylene respectively, all treated with the same insecticide (deltamethrin), over 3 years of field use in North-East Tanzania.

### Study objectives

To undertake a large scale community-based Phase III evaluation comparing the insecticidal efficacy and durability of polypropylene LifeNet® LN against a deltamethrin-treated polyester LN with full WHOPES approval (PermaNet® 2.0) and a deltamethrin-impregnated polyethylene LN over 3 years of continuous use in a malaria endemic setting of North-East Tanzania.

Specific objectivesTo assess the insecticidal efficacy of a deltamethrin-treated LN made of polypropylene (LifeNet®) compared with deltamethrin-treated LNs made of polyester and polyethylene over 3 years of household use.To determine the durability (survivorship and fabric integrity) of a deltamethrin-treated LN made of polypropylene (LifeNet®) compared with deltamethrin-treated LNs made of polyester and polyethylene over 3 years of household use.To assess washing habits and frequency of LN washing by householders over 3 years of household use.To document and compare community perceptions of all three LNs by participants over 3 years of household use.

All objectives will be investigated following standardized WHO guidelines for laboratory and field testing of LNs [28] and durability monitoring under operational conditions [4].

## Methods/Design

### Study area and participant recruitment

The trial will be conducted in four villages (Magila, Kibaoni, Ubembe and Misongeni) situated in Muheza District, Tanga region of North-East Tanzania (5^o^ S, 39^o^ E) (Fig. 1). The district encompasses an area of approximately 4922 km^2^, ranging from a coastal plain at sea level to the Usambara mountains at 1500 m. The climate is tropical with dense forest covering the mountain region. Muheza District has four administrative divisions comprising 33 wards with 135 villages, mainly inhabited by subsistence farmers. The population of Muheza District was 204,461 residents in 2012 with an annual growth rate of 2.2% [29]. The average population size of a typical village is approximately 1700 inhabitants among 450 households.

**Fig. 1 Fig1:**
[figure not shown]
Map showing 18 study hamlets identified in Muheza District (*arrow*), Tanga region (*shaded*), North-East Tanzania

Muheza District is highly endemic for malaria with transmission occurring throughout the year with two seasonal peaks during and after the long rainy season from July to August and the short rainy season from December to January [30]. During the rainy seasons *Anopheles gambiae* sensu stricto and *An. funestus* are the most abundant malaria vectors [31]. During the dry season *An. funestus* remains fairly common but *An. gambiae s.s.* numbers decline [31–33]. The lymphatic filariasis vector and nuisance mosquito *Culex quinquefasciatus* is abundant from December to June. Historically, Muheza District has not been subjected to IRS but did receive LNs during nationwide UCC distributions [23, 24].

Villages or groups of larger hamlets will be selected in collaboration with the District Assembly and District Medical Officers (DMOs) on the basis of population size, number of households, willingness to participate, road accessibility and proximity to the National Institute for Medical Research (NIMR) laboratory and insectary facilities of Amani Medical Research Centre and with no other ongoing vector control interventions at time of recruitment.

### Study design, randomization, blinding and bias

This will be a prospective cluster randomized controlled, equivalence trial with nets as the unit of observation. Following household enumeration, global positioning system (GPS) coordinates will be recorded and baseline socio-demographic and economic data, including age, sex, occupation, education, household wealth, sleeping habits and number of spaces, ownership and use of other mosquito nets and net preferences (size, colour, shape and washing habits) will be collected using a standardized questionnaire.

Once baseline chemical analysis of LNs is completed and confirmed to be within WHO specifications, the nets will be distributed. The monitoring period will be 3 years, beginning August 2014 (Table 1). At study onset, equal numbers of households from eighteen hamlets will be randomized to the three study arms. All participating households in a specific hamlet will be provided with the same type of LN to achieve universal coverage, assuming an average of 4.0 sleepers and 2.1 sleeping places per household. To ensure all members in a participating household are using the same LN brand, any existing nets will be removed and replaced by study LNs. All LNs will be issued free of charge to recipients. Net users will be encouraged to retain the LNs they are given and not to sell or exchange them with other study participants. If for any reason an owner stops using a net, they are requested to volunteer the reason and to store the net for later inspection by investigators.

**Table 1 Tab1:** Timetable of study activities

Activity	Pre-Intervention	Post Intervention monitoring period (months)						
		0	6	12	18	24	30	36
Community selection, sensitization and consent	X							
Baseline census and household survey	X							
LLIN distribution	X							
Cross-sectional surveys: bioefficacy assays	X	X	X	X	X	X	X	X
Cross-sectional surveys: chemical assays	X			X		X		X
Cross-sectional surveys: fabric integrity		X	X	X	X	X	X	X
Cross-sectional surveys: fabric strength		X	X	X	X	X	X	X
Cross-sectional surveys: community practices		X	X	X	X	X	X	X
Cohort surveys: household survivorship and fabric integrity		X	X	X		X		X
Insecticide resistance monitoring	X			X		X		X
Adverse events monitoring		X						

To assess bioefficacy (insecticidal activity measured by mosquito knock-down and mortality), deltamethrin content (g/kg and mg/m^2^), fabric integrity (location and size of holes) and fabric strength, a series of cross-sectional surveys and destructive sampling of LNs will be undertaken on randomly selected nets every 6 months for WHO cone bioassays, yearly for insecticide analysis using gas chromatography (GC), and physical integrity (hole index) every 6 months up to 18 months and then annually. A longitudinal cohort of LNs will be followed every 6 months to measure survivorship (net attrition rate) and loss of fabric integrity. Community attitudes and practices of LN use will be assessed every 6 months using the standard WHO LN durability monitoring questionnaire. Impact of the interventions on insecticide susceptibility of major malaria vectors will be evaluated each year in study villages and neighboring control areas. Study participants will also be monitored for possible adverse events during the first month post LN distribution using a structured questionnaire. A schematic representation of the trial is shown in Fig. 2.

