### LN products and distribution

LifeNet® LN is a net with deltamethrin-incorporated into 100 denier polypropylene filaments at 8.5 g AI/kg or 340 mg/m^2^ (Bayer CropScience, Germany) [26]. It has undergone a WHO generic risk assessment model and does not pose undue hazards to the user when used as instructed [34]. LifeNet® LN has attained a WHO interim recommendation following successful Phase II experimental hut trials in 2011 [26] and will be granted a full WHO recommendation following successful completion of a Phase III evaluation.

Under WHOPES guidelines, LifeNet® LN efficacy and durability will be compared to a LN which has already completed Phase III evaluations successfully. PermaNet® 2.0 LN (Vestergaard Franden, Switzerland) is a multifilament polyester net treated with deltamethrin to a target concentration of 55 mg/m^2^, bound in a wash-resistant resin coating that received full recommendation in 2008 and is widely used by NMCPs [35]. Because LifeNet® LN introduces a novel polymer to the range of textile materials currently favoured for nets it is important to test the polypropylene LN against net products representative of different material types. In addition to a polyester LN typified by PermaNet® 2.0 LN, LifeNet® LN will be compared with a net brand submitted to WHOPES, made from polyethylene monofilaments incorporated with deltamethrin to a target concentration of 63 mg/m^2^ (Table 2). This study will provide a unique opportunity to evaluate the relative durability and residual efficacy of three LNs each made from different textiles, containing the same insecticide (deltamethrin), following two different treatment methods (incorporation and coating).

**Table 2 Tab2:** Characteristics of three LN brands distributed in the study

LLIN Brand	Manufacturer	Fabric	Deltamethrin Concentration	A.I. Application	Denier	Av. Mesh Size Per cm^2^	Bursting Strength (kPa)	Colour	Size (cm)	WHOPES Recommendation	References
LifeNet®	Bayer CropScience, Germany	Polypropylene	340 mg/m^2^	Incorporated into fibres	100	21–29	450	White	W190 × L180 × H 150	Interim (2011)	[26]
PermaNet® 2.0	Vestergaard Frandsen, Switzerland	Polyester	55 mg/m^2^	Resin coating	100	24	250–350	Blue	W190 × L180 × H 150	Full (2008)	[35]
Polyethylene LN	Bestnet A/C, Denmark	Polyethylene	63 mg/m^2^	Incorporated into fibres	110	21	540	White	W190 × L180 × H 150	Withdrawn (2014)	[46]

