### Sample size rationale

Sample size calculations are based on detecting differences in LN insecticide efficacy and physical durability (attrition rate and fabric integrity) between the three comparison nets over a 3 year period, while allowing for destructive sampling and replacement of LNs for biological and chemical efficacy assays and an expected attrition rate of 20% per year for each product.

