#### Cohort surveys: household survivorship and fabric integrity

During the longitudinal cohort study, 250 LNs from 125 households per study arm will be monitored after 6 months and then followed at annual intervals to evaluate net survivorship and attrition and loss of fabric integrity over 3 years. All 250 LNs will be assessed for survivorship and 150 (approximately one per household) will be examined for loss of fabric integrity. Assuming an attrition rate of 20% per year, 200 households will participate in the cohort study (an additional 640 LNs), allowing a 12% point difference in LN attrition rate to be detected.

A total of 2300 nets per study arm will be required for both cross-sectional and cohort surveillance.

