Fabric integrity during the field trial will be assessed using various criteria: 1) the proportion of LNs with holes (total number of each LN product with at least one hole of any size, divided by the total number of each LN product surveyed); 2) the proportional hole index (calculated by weighting each hole by size and summing for each net (Table 3) [28]; and 3) hole area and circumference. For each LN product, fabric integrity indices will be compared by analysis of variance for normally distributed data or the Kruskal-Wallis test or Poisson regression for non-parametric data.

Multivariate regression analysis will be used to identify factors that influence LN durability and community acceptability of each net product, using variables derived from household questionnaire data.

Fabric strength and resistance-to-damage tests [37] will be based on bursting strength and wounded bursting strength (EN ISO 13938-2, a measure of tear resistance), hook tensile strength (ISO 13934-2), snag strength (adapted EN 15598), abrasion resistance (ISO 12947:1998) and hole propagation tests (multi axial loading of wounded bursting strength test) of LNs collected from the field and will be correlated with LN durability indices.

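### The trial is labelled an equivalence trial but is sized to detect differences and states no margin or interval rule, so it cannot support an equivalence conclusion and a non-significant difference could be misread as one

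*Protocol article*

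**What the plan says.** The label appears twice. The abstract (Methods) says "This is a prospective three-arm household randomized, equivalence trial of LNs in Tanzania, with nets as the unit of observation", and Study design, randomization, blinding and bias says "This will be a prospective cluster randomized controlled, equivalence trial with nets as the unit of observation".

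The operative text asks another question:

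- **Sample size rationale:** "Sample size calculations are based on detecting differences in LN insecticide efficacy and physical durability". The cohort subsection describes its size as "allowing a 12% point difference in LN attrition rate to be detected".
- **Data analysis, fabric integrity:** "fabric integrity indices will be compared by analysis of variance for normally distributed data or the Kruskal-Wallis test or Poisson regression for non-parametric data".
- **Data analysis, bioefficacy:** after 3 years, at least 80% of a candidate product's sampled nets must pass the cone or tunnel criteria. This is an absolute threshold for each product.
- **Data analysis, survivorship and attrition:** the measures are defined, but no between-arm test is named.
- **Discussion:** the trial's primary purpose is to compare the relative field durability of the three polymers.

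On the comparators, the Background says the candidate is "compared to two WHOPES recommended LNs made from polyester and polyethylene respectively". Table 2 lists the polyethylene net's recommendation as "Withdrawn (2014"), and the text beside it says only that this net had been submitted to WHOPES. Study objectives gives full approval to the polyester net alone.

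**The concern.** An equivalence conclusion needs a margin set in advance and a rule that the confidence interval for the difference must lie inside it. Without these, the only between-arm result that could be attached to the label is a failure to reject no difference, and that becomes easier to obtain as the samples get smaller or noisier.

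The question put to the trial also points the other way. The Background reports the manufacturer's claim of improved durability, and the abstract's Discussion wants to know which polymer gives the longest replacement interval. Both ask about differences.

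The word carries weight here. The Discussion notes that some nets obtained full WHO recommendations on the basis of equivalence, and this trial is meant to inform a recommendation and procurement policy.

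**Working it through.** **1. The passages side by side.** The label says equivalence. The sample size basis, the one between-arm effect size given (12 points, described as detectable), the named between-arm tests and the stated primary purpose all concern differences. The bioefficacy rule is neither a difference test nor an equivalence test. No margin is given for any outcome.

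**2. The plan's own figure.** Inputs from the article: 250 cohort nets per arm, a 12-point detectable difference, and "an expected attrition rate of 20% per year for each product". The article gives no alpha, power or reference time for the 12 points, so the figure cannot be strictly reproduced. Assumptions: two-sided 5%, 80% power, independent nets, and either the one-year rate of 20% or 3-year survival of 0.8³ = 51.2%.

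n per arm = [1.96·√(2p̄(1−p̄)) + 0.842·√(p₁(1−p₁) + p₂(1−p₂))]² / d²

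- 51.2% v 63.2%: (1.371 + 0.585)² / 0.0144 = 266 nets
- 20% v 32%: (1.216 + 0.517)² / 0.0144 = 209 nets

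Solved the other way, 250 nets detect 12.4 points from 51.2% and 10.9 points from 20%. The 12 points therefore behave like a difference-detection calculation, which agrees with the article's own description.

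**3. What non-significance would mean in the cohort.** Power = Φ[(d − 1.96·SE₀)/SE₁], with SE₀ pooled, SE₁ unpooled and n = 250 per arm.

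| True 3-year survival | SE₀ | SE₁ | (d − 1.96·SE₀)/SE₁ | Power | Non-significant |
|---|---|---|---|---|---|
| 51.2% v 59.2% | 0.0445 | 0.0443 | −0.16 | 44% | about 56% |
| 51.2% v 63.2% | 0.0443 | 0.0439 | 0.76 | 78% | about 22% |

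Real gaps of this size would often go undetected, so non-significance is not evidence of equivalence.

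**4. If 12 points were used as an equivalence margin (my assumption).** Two one-sided tests, true difference 0, 80% power:

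n per arm = 2p(1−p)(z₁₋α + 1.282)² / 0.12²

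- p = 51.2%, α = 0.05 per side: 0.4997 × 8.564 / 0.0144 = 298
- p = 51.2%, α = 0.025 per side: 0.4997 × 10.508 / 0.0144 = 365
- p = 20%: 0.32 × 8.564 / 0.0144 = 191, and 0.32 × 10.508 / 0.0144 = 234

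The planned 250 falls short at 51.2% (power 70% or 53%) and suffices at 20%. Whether the cohort is large enough for equivalence is undetermined until an outcome, time point and margin are named. Allowing for clustering would raise all these numbers.

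**The case against.** The article condenses a fuller protocol, and an analysis plan may exist that supplies a margin. That would answer a mere omission. It does not answer this point, because the article states a sample size basis and that basis is the opposite of what the label requires.

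Several stronger readings are tempting, and the article does not support them:

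- **That non-significance will be read as equivalence.** No passage says so. The rules that are written point to the absolute bioefficacy threshold and to relative durability. The risk is that a result could be misread.
- **That the whole trial is analysed by difference tests.** These are named only for the fabric integrity indices.
- **That the trial is too small for equivalence.** Step 4 shows that this depends on a margin and a rate the article does not fix.
- **That 50 nets per arm at 36 months set a floor of about 16 points on any bioefficacy margin.** The 95% half-width, 1.96·√(2p(1−p)/50), is 15.7 points at an assumed 80% pass rate but 11.8 at 90%, so it is no general limit. At 80%, a margin giving 80% non-inferiority power (one-sided 2.5%, true difference 0) would be about (1.96 + 0.84) × 0.08 = 22 points. The article plans no between-arm bioefficacy test in any case.
- **That the polyethylene arm is worthless because its recommendation was withdrawn.** Its stated role is to represent a material type, and the approved reference is already the polyester net alone. The wording conflict is real but minor.

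**Conclusion.** The contradiction stands on the stated text. The trial carries an equivalence label, but its sample size, its named between-arm tests and its stated primary purpose are about differences, its bioefficacy rule is absolute per product, and no margin or interval rule is given. It cannot support an equivalence conclusion as described, and a non-significant difference could be misread as one.

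The cohort figures show the scale: about 56% non-significant for a true 8-point gap in 3-year survival and about 22% for 12 points. They rest on a two-sided 5% test, independent nets and 20% annual attrition compounded over 3 years. Hamlet or household clustering would make non-significance more likely still.

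The defect lies in the label and in what may be claimed from it. Data collection and the 80% bioefficacy rule are untouched.

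**What to change.** - Delete the word equivalence in the abstract and in the study design section. Describe two-sided comparisons of durability among the three nets, reported as differences with 95% confidence intervals.
- Keep the absolute 80% bioefficacy rule per product. Report any between-arm bioefficacy differences with confidence intervals only.
- State that a non-significant difference will not be interpreted as equivalence.
- If a non-inferiority or equivalence claim is still wanted, make it only against the polyester reference, with a named outcome and time point, a justified margin and a confidence-interval rule, all fixed before the 36-month data are examined. Monitoring is already in year 2, so the record should say that the margin was set after earlier surveys had begun. Do not add a general statement about the smallest margin that 50 nets can show.
- Correct the Background's description of both comparators as recommended so that it agrees with Table 2.

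The cost is wording only. The trial gives up an equivalence claim that it has no rule to support.

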WHOPES Phase III bioefficacy guidelines for LNs are currently based on retention of bioefficacy rather than physical durability. To obtain a WHOPES full recommendation at least 80% of the LNs surviving 3 years of household use in malaria endemic countries must retain sufficient insecticidal activity to induce 80% mosquito mortality in bioassay tests [28]. Four brands of LN have already achieved this criteria: polyester nets, PermaNet 2.0® and Interceptor® [35, 40], and polyethylene nets, Olyset® and DuraNet® [41, 42]. A further four LNs have obtained WHO full recommendations on the basis of equivalence to the aforementioned brands, and a further eight have obtained WHO interim recommendation after demonstrating bioefficacy in Phase II experimental hut trials [25]. While most brands of LN may achieve the requisite levels of bioefficacy, it is much less clear whether all types of net can physically withstand the wear and tear of 3 years of household use. LN survival will depend on the environment and household conditions of use. A LN stretched over a rustic wooden bed in a cramped traditional mud house will not last as long as a properly fitted LN draped over a bespoke net frame in a rodent free home. The duration of the mosquito season will also affect LN longevity and usage, and this will differ between the tropics and subtropics, highlands and lowlands, and coastal and plain areas [4, 15]. In practice, few brands of LN have undergone rigorous longitudinal monitoring. The first LNs to obtain WHOPES full recommendation - polyester PermaNet 2.0® LN and polyethylene Olyset® LN - were the subject of annual cross-sectional surveys of random samples of nets [35, 42] across a number of countries after 1–3 years of use rather than longitudinal monitoring of a documented cohorts of nets [28]. In these surveys it was noted that net integrity (hole index) reached a steady state after 2 years of use indicating that LNs with higher hole indexes were being discarded and not surviving to 3 years. In these countries only one brand of net had been distributed. Unless different types of LNs are tested in the same location, in parallel, in household randomized trials, it will be difficult to determine their relative durability under field conditions. Few LN brands have been evaluated against one another in this way. A recent exception was a household randomized trial in Cambodia between polyethylene Netprotect® LNs and polyester PermaNet 2.0® LNs [43]. Net survivorship exceeded 90% in the first 2 years but after 3 years decreased to ~60% for both LNs, indicating that nets of either material were unable to last much longer than 2 years. It is therefore appropriate that the proposed trial of a longer lasting polypropylene LN is assessed alongside and against polyester and polyethylene LNs over 3 years of field use.

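### The unit of randomisation is stated two ways (hamlet or household), and neither the 12-point detectable difference nor the named fabric-integrity tests show any allowance for clustering

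*Protocol article*

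**What the plan says.** The Abstract (Methods) says: "This is a prospective three-arm household randomized, equivalence trial of LNs in Tanzania, with nets as the unit of observation". It adds that "all sleeping spaces in a given household will be provided with one type of net", so on this reading the household is the allocated unit.

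The section Study design, randomization, blinding and bias says: "This will be a prospective cluster randomized controlled, equivalence trial with nets as the unit of observation". It continues: "At study onset, equal numbers of households from eighteen hamlets will be randomized to the three study arms", and then: "All participating households in a specific hamlet will be provided with the same type of LN to achieve universal coverage". If the last sentence holds, net type cannot vary within a hamlet and the hamlet is the allocated unit. The number of hamlets per arm is not given.

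The Sample size rationale adjusts for yearly attrition of 20% and for destructive sampling. For the cohort it plans 250 nets from 125 households per arm, 150 of them examined for fabric integrity, "allowing a 12% point difference in LN attrition rate to be detected". It gives no significance level, power, reference attrition rate, time point, ICC or design effect.

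Under Data analysis, "fabric integrity indices will be compared by analysis of variance for normally distributed data or the Kruskal-Wallis test or Poisson regression for non-parametric data". No term for hamlet or household is mentioned. No comparative test is named for attrition or survivorship.

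**The concern.** The two descriptions lead to different trials. With hamlet allocation there are at most eighteen independent units, and each arm's result rests on a handful of hamlets. With household allocation there are 125 cohort households per arm and much more independent information. A reader cannot tell which trial was run, and the analysis cannot be specified until that is settled.

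The Discussion says that net survival depends on the environment and on household conditions such as the type of house and bed and the presence of rodents. Neighbouring houses plausibly share these, and two nets in one house certainly share many of them. If that correlation is ignored, standard errors are too small and a difference between hamlets can be read as a difference between polymers. Comparing the field durability of the three polymers is what the Discussion gives as the trial's primary purpose, and the Abstract says the findings will guide procurement.

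**Working it through.** **Inputs from the protocol.** 250 cohort nets per arm in 125 households, two per household; 150 of these examined for fabric integrity; cross-sectional surveys of 30 nets per arm, one per household, with 100 nets per arm scored for integrity at 24 and 36 months; eighteen hamlets; attrition 20% per year.

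**Assumptions.** Two-sided 5% and 80% power. Reference attrition either 20% (one year) or 1 − 0.8³ = 48.8% (three years). Six hamlets per arm (18/3). Hamlet ICC 0.005 to 0.10; within-house correlation 0.1 to 0.5.

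**Step 1: the plan's own figure.** The detectable difference d = |p1 − p2| solves

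d·√n = 1.96·√(2·p̄·q̄) + 0.84·√(p1·q1 + p2·q2).

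With n = 250 independent nets and p1 = 0.488, trying p2 = 0.612 gives p̄ = 0.55. The right side is 1.96·√0.495 + 0.84·√0.487 ≈ 1.97, and 1.97/√250 ≈ 0.124. So d is 12.4 points. From 20% upward it is 10.9 points, and from 20% downward 9.0. The stated 12 points lies near the top of this range. It cannot be formally reproduced, because the protocol gives none of the settings.

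**Step 2: hamlet allocation, attrition.** About 250/6 = 41.7 cohort nets per hamlet. Design effect DE = 1 + (41.7 − 1)·ICC; effective n = 250/DE. Reference attrition 48.8%, compared with a higher rate:

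| ICC | DE | Effective n | Detectable difference | Power for 12 points |
|---|---|---|---|---|
| 0.01 | 1.41 | 178 | 14.7 points | 62% |
| 0.05 | 3.03 | 82 | 21.3 points | 34% |
| 0.10 | 5.07 | 49 | 27.0 points | 22% |

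These are normal-theory figures. With 12 hamlets in a pairwise comparison (10 degrees of freedom), power falls further, to about 54–55%, 29–30% and 19–20%. The favourable corner is 20% against 32% with ICC 0.005: DE is 1.20, effective n 208 and power 79.8% (72% with 10 degrees of freedom).

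**Step 3: household allocation, attrition.** With two nets per house, DE = 1 + ρ. At 48.8% attrition, ρ of 0.1, 0.3 and 0.5 gives DE of 1.1, 1.3 and 1.5, and detectable differences of 13.0, 14.1 and 15.2 points. At 20% attrition the corresponding figures are 11.5, 12.5 and 13.5 points. A survey that takes one net per house has almost no design effect on this reading.

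**Step 4: fabric-integrity tests as named.** For a pairwise net-level test that ignores hamlets, the approximate true type I error is 2·(1 − Φ(1.96/√DE)), with m nets per hamlet and DE = 1 + (m − 1)·ICC. Under hamlet allocation:

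| Sample per arm | m | ICC 0.01 | ICC 0.05 | ICC 0.10 |
|---|---|---|---|---|
| 150 cohort nets | 25 | 7.8% | 18.6% | 28.8% |
| 100 nets (24 and 36 months) | 16.7 | 6.8% | 14.2% | 22.1% |
| 30-net surveys | 5 | 5.5% | 7.4% | 9.8% |

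The first row, for example, uses DE of 1 + 24·ICC = 1.24, 2.20 and 3.40.

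**The case against.** The best defence is that hamlet allocation is not established. The design section equalises households rather than hamlets, the Abstract says household randomised, and six hamlets per arm is only 18/3. Under household allocation the loss is modest and the 30-net surveys are nearly unaffected. This stands, and it is why every figure above is tied to a reading.

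A reader might infer from the match in Step 1 that no design effect was used. The documents do not show that. At 20% against 32%, about 209 independent nets per arm suffice, so 250 would leave room for a design effect of about 250/209 = 1.2. At 48.8% even independent nets would need 266 to 269. The base number is also unsettled, since 200 households (640 nets) are to be enrolled in the cohort. What can be said is that no allowance is stated.

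A reader might also carry a type I error over to the attrition comparison, or say that repeat visits to the same net are treated as independent. The protocol names no test for attrition, and it does not say that visits are pooled; a separate comparison at each survey fits the text equally well.

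The Discussion's remark that, without side-by-side testing "in household randomized trials, it will be difficult to determine their relative durability under field conditions", is a general argument about evaluating brands, so it adds little on how this trial was allocated. The WHO bioefficacy criterion is a fixed threshold (80% of nets passing) and is not judged by the tests discussed here.

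Finally, an unseen analysis plan may well specify random effects or robust variances. That would cure the tests. It would not cure two conflicting statements of the design, or a detection limit printed without its assumptions.

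**Conclusion.** The contradiction on the unit of randomisation is in the text and needs no assumption. Also in the text is that the sample-size section states no allowance for clustering and that the named fabric-integrity tests carry no hamlet or household term, although nets are clustered on either reading.

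The size of the consequence depends on the reading. If hamlets were allocated, the 12-point claim is unsupported for most plausible ICCs, with a low attrition rate combined with a very small ICC as the exception, and the cohort fabric tests run as written would be clearly anti-conservative. If households were allocated, the claim is mildly optimistic at three-year attrition and may hold at 20% attrition with weak within-house correlation. The magnitudes rest on an assumed significance level, power, reference rate, ICC and six hamlets per arm, none of which the protocol gives. It would go too far to say flatly that the stated detection limit is not delivered.

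**What to change.** 1. Reconcile the Abstract with the design section: name one unit of randomisation and state the number of hamlets per arm.
2. Replace the single 12-point figure with a range of detectable differences, giving the significance level, power, reference attrition and its time point, and the ICC values used.
3. If hamlets were allocated, compare arms through hamlet-level summaries, or through mixed models with random effects for hamlet and household, using small-sample degrees of freedom (18 − 3 = 15 overall, 12 − 2 = 10 pairwise if six per arm). If households were allocated, allow for household clustering. In either case add a random effect for net if visits are pooled.

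The cost is wording and analysis code, and a less favourable detectable difference. The net identification codes already record village, hamlet and household, so no extra nets, visits or data items are needed.
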